#### 2.2.3. Variables 

All collected variables for the study are shown in Table 2. 

### 2.3. Anthropometric and Others Clinical Variables

In the pre-randomization stage, collection of sociodemographic data of each child including age, gender, any comorbidity, and findings from physical examination, including the degree of tonsil hypertrophy, Mallampati score, and maxillomandibular profile will be recorded. Anthropometric data will be obtained after each of the two PSG tests. We will measure in each subject, weight, height, body mass index (and percentiles), neck and waist circumference, and arterial blood pressure (ABP). ABP will be measured 3 times after 5 min of resting in the supine position using standardized and validated automatic sphygmomanometer (Spacelab type) and using the appropriate arm cuff size for the child.

### 2.4. Sleep Studies

#### 2.4.1. Polysomnography in Sleep Laboratory (PSG)

An overnight PSG will be performed at baseline and at six months based on the American Academy of Sleep Medicine guidelines [53], the recent European Respiratory Society recommendations [54], and the Spanish Sleep Apnea Recommendations [55]. EEG recordings will include six electroencephalographic electrodes: two frontal (F3–F4), two central (C3–C4) and two occipital (O1–O2) locations, referred to contralateral mastoids (A1–A2) and adopting the 10–20 rules of international EEG system. We will include one ground electrode and another reference electrode (Cz). The electromyogram will be obtained using two chin electrodes and the electrooculogram (EOG) will be recorded employing two different electrodes placed above the left and right outer eye cantus. The different sleep stages: N1, N2, N3 (NREM sleep), and REM will be scored; arousals, oxygen saturation (SaO_2_) and apneas and hypopneas were identified (Table 3) using standardized guidelines [56,57,58,59]. The PSG will be considered as valid if total recording time is ≥300 min and includes at least 180 min of actual sleep. All the technicians scoring PSG will be blinded to the results of the study. Although polysomnographic recording equipment will be different in each participating center, standard scoring rules will be implemented [53,56,57,58,59]. The morning after testing, parents will be requested to fill out a subjective questionnaire about the quality and quantity of that night’s child sleep. Scoring of respiratory events will be conducted using the same rules in PSG and HRP (see below). 

#### 2.4.2. Home Respiratory Polygraphy (HRP)

Respiratory events will be scored using the same criteria in both HRP and PSG, except for the presence of a respiratory arousal which will only be identified in the PSG. In addition, derivation of AHI will be based on total recording time in HRP and on total sleep time in PSG.

The HRP will be scheduled based on the usual bedtime of the child as obtained from the sleep questionnaire. A recommended time in bed during the HRP of ≥8 h will be requested from participants. A HRP recording will be deemed valid if recording duration is ≥5 h. In both HRP and PSG recordings, sections with artifacts or poor signal will be excluded from analysis. In the event that a HRP or PSG is not valid, it will be repeated within the next 7 d. 

The HRP system to be implemented is the Apnea Link Air (Resmed^®^ Spain, (Madrid, Spain) (Figure 2). This is a type III home sleep apnea testing (HSAT) device that has been validated in the diagnosis of OSA in adults, but not in children [34,35,36]. ApneaLink Air measures being recorded include nasal airflow and snoring using a nasal pressure cannula, blood oxygen saturation, and heart rate by pulse oximetry, and respiratory effort using a thoracic piezoelectric chest belt. The device is small and light (~50 g; 125 × 60 × 30 mm). The software allows to carry out both automated and manual analyses.

Parents will be provided with the device to take home with a prior detailed explanation on how to operate it, along with careful instructions on the correct placement of the device sensors and monitoring of the child. Parents will also perform multiple trials to become comfortable in the device operation guidelines. When the patients return the device the following day, the raw data files will be transferred to a computer and scored automatically and manually by an experienced sleep technologist, while excluding artifact periods.

In an effort to assess the inter-scorer variability between centers, all the recordings for both PSG and HRP will also be scored by the same technician in the study reference center.

### 2.5. Questionnaires

Several questionnaires will be included as follows:(a)Sleepiness rating log [60](b)Pediatrics sleep questionnaire (PSQ) [61](c)“Bears” (Bedtime, Excessive daytime sleepiness, Awakening, Regularity, Sleep-disordered breathing) test [62](d)“Children´s Sleep Habits Questionnaire—CSHQ” and restless legs syndrome questionnaire [63](e)Kiddy-KINDL quality of life of children and young people test (version for parents) [64](f)“Pictorial-Based Declarative Memory Questionnaire” (PDMQ [65]. This test consists to children were then shown a booklet containing a series of 30 colorful pictures of common animals that are highly familiar to children (Figure 3). The child initially identifies the animal being shown and then the investigator also names each animal as further corroboration of the adequate recognition of the animal on each picture, while pointing them out page after page. Subjects were allowed 10 s to look each animal picture. The book was then closed, and the subjects were given 2 min to freely recall any of the animals they could remember without looking at the pictures.

All tests will be completed on two occasions, during the initial and follow-up PSG in the morning after the sleep study. Moreover, the PDMQ will be performed twice, i.e., the night before beginning the sleep study and the morning after each PSG.

### 2.6. Urine Sample Collection, Processing and Analysis 

Morning first void mid-stream urine samples will be collected after each of the two PSG in two 50 mL aliquots that will be immediately stored at −70 degrees until their analysis in the laboratory of the Department of Child Health at the University of Missouri School of Medicine at Columbia, MO, USA. After appropriate aliquoting and initial centrifugation and vortexing, isolation of exosomes will be performed as previously reported [66,67]. Circulating miRNAs are in body fluids such as in urine and are packaged in secreted urinary extracellular vesicles which protect them from degradation. The exosomal fraction will be extracted using ultracentrifugation and size exclusion chromatography harvested from 20 mL urine, and will be subjected to further characterization using western blotting and transmission electron microscopy, and quantification based on nanoparticle tracking analysis using NanoSight NS300 (405 nm laser diode) according to the manufacturer’s protocols (Malvern Instruments Inc.). The Norgen Biotek’s Urine Cell-Free Circulating RNA Purification Maxi Kit (Cat. 56600) will be used to isolate miRNAs from 50 mL urine samples according to manufacturer’s instructions. The mirVana miRNA Isolation Kit (Life technologies, AM1560) will be used for miRNA isolation from the urinary exosomes. Exosomes are lysed in the equal volume of sample/lysis buffer and further processed according to manufacturer’s protocol. RNA concentration and quality will be assessed using Nanodrop 1000 spectrophotometer (Thermo Scientific), and Agilent RNA 6000 Nano Kit, Agilent Small RNA kit on Agilent 2100 Bioanalyzer (Agilent Technologies). cDNA synthesis and qPCR will be performed using the TaqMan Advanced miRNA cDNA Synthesis Kit (Applied Biosystems, A28007) according to manufacturer’s instructions. MicroRNA advanced TaqMan assays will then be used for qPCR and results will be analyzed with web browser-based Applied Biosystems™ Real-Time PCR Analysis Modules.

### 2.7. Ethics and Safety Concerns

This study is not anticipated to result in any meaningful health risks for children, except for the discomfort of performing two consecutive sleep tests within a week of each other. In the HRP test, the children will sleep in their usual bedroom at home and family member returns the equipment the next day. Questionnaires are completed the night of the PSG in the sleep center and urine collection is obtained then in the morning. The second six-month sleep PSG will be performed following the usual clinical treatment protocol for those children with OSA, but reflect an additional PSG for those in whom OSA was not present in the initial study. As indicated above, the project was approved by the ethics committees of each of the participating centers. The parents will sign an informed consent, and for children ages > 7 years, an informed assent will be also signed by the child. Finally, although the study lacks any anticipated risks, all subjects will be covered by the general insurance policy of the Osakidetza-Basque Health Service and by the National Health System.

## 3. Statistical Analysis

All data will be collected in an electronic Case Report Form (eCRD).

Sample size: We estimated a prevalence of 60% of symptomatic children with an AHI > 3 events/h. Thus, a total of 320 eligible subjects are needed assuming a 10% attrition, and a difference in effectiveness between PSG and HSP that will not exceed 9% (α = 0.05 and a β coefficient of 90%). Subjects who refuse to participate and those identified as ineligible will be recorded.

Cost effectiveness analysis is proposed as a non-inferiority study, comparing baseline PSG and 6-month follow-up PSG derived AHI (alpha 0.05; 80% power). It is assumed that the non-inferiority limit is 0.45 units of AHI, i.e., the PSG AHI at 6 months follow-up for therapeutic decisions made with either the PSG or the HPR findings, with a cut-off AHI set at 3.6 ± 2.0 events/h [38]. Considering attrition, 155 subjects will be required to complete the study in each arm (PSG and HPR).

Data will stored in a networked Deductive Database (BBDD) specifically designed and maintained for the study to this study. Statistical analysis will be performed with SPSS package (IBM, New York, NY, USA version 22.0). The measure of the overall agreement between the different categories of the AHI as measured by PSG and HRP, in their automatic and manual analysis, will be assessed by establishing the diagnostic accuracy of the scores obtained by each of the systems. Different categories will be established according to the OSA diagnostic criterion cut-off (AHI > 3 events/h). The HRP discriminatory capacity for the diagnosis of exclusion and confirmation of OSA will be estimated according to different severity AHI cut-off values using ROC curves, area range under the curve and subsequent Bayesian analysis, as previously reported [15,68]. Therapeutic decisions made with PSG will be compared with decisions made with HPR, with data being interpreted independently by all participating centers and compared with each other using Cohen’s Kappa. Further analyses will be carried out on both arms based on intent to treat. In cases considered as attrition, imputation values will be allocated using multiple regression.

Financial analyses will include only direct costs: (a) Costs of testing (HPR and PSG) including the following items: personnel (technical, medical, nurses, and secretaries); amortization of HRP and PSG equipment based on the assumption of 200 studies per year for 5 years; fungible material; and costs across the medical center as a whole; (b) Cost of patients: cost of transfer and return patients to hospital for PSG and HRP; (c) Cost of PSG and HRP test repetitions as needed due to technical failure or unsatisfactory test; (d) Cost of CPAP treatment (Figure A1), adenotonsillar surgery, orthodontics, and medical treatment; and (e) cost of health care after randomization (number of visits in primary care, specialized care and emergency or hospital care excluding those visits related to adenotonsillar surgery; drugs (trade names) and inpatient costs (number of patients and hospital days).

Costs associated with each of the diagnostic approaches will be assessed against the effectiveness of the primary variable (AHI) using Bayesian cost-effectiveness analysis techniques. The decision-making measures studied will consist of the cost-effectiveness ratio of each treatment, the incremental cost-effectiveness ratio (ICER), the cost-effectiveness plane, the net profit of each treatment, the incremental net profit (NB) and the cost-effectiveness acceptability. We will apply sensitivity analysis using decision model simulation methods. Specifically, we have developed a probabilistic sensitivity analysis of the cost-effectiveness ratio by specifying uncertain parameter distributions in our decision model. To estimate probability intervals, we categorize numerical values of ICER in order to consider preferences on the cost-effectiveness plane.

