## 4. Study Significance

Currently, the gold standard approach to the diagnosis of OSA in children remains a PSG in the laboratory [12]. However, the emergence of a large array of home-based technologies and the successful implementation of HST in adults has prompted substantial interest in expanding the role of HST to the pediatric population. Such need is all the more pressing considering on the one hand the elevated prevalence of children who habitually snore and are therefore at-risk for OSA [69,70,71,72,73], and on the other hand the paucity of pediatric sleep laboratories, the scarcity of pediatric sleep medicine physicians, the inconvenience for the child and their family, the high costs in labor, and of the facilities underlying PSG testing. However, HST approaches are not yet extensively validated in children, and their usefulness and financial advantages have not been thoroughly explored despite the relatively large number of published studies comparing PSG and HST.

The proposed study incorporates not only the validation in a real life setting of a HST approach as a diagnostic tool, but also includes an assessment of its robustness in the clinical decision making of when to provide clinical treatment and when to abstain from a therapeutic intervention. Furthermore, it will examine not only the comparative outcomes obtained with HST and PSG, but will also evaluate cognitive outcomes as illustrated by a declarative memory test [65]. In addition, it will provide estimates of feasibility of automatic scoring that should alleviate the laborious burden of manual scoring of HST in children. Importantly, economic assessments of the HST relative to the PSG will be conducted.

Finally, a simple and non-invasive method such as the proposed examination of exosomal miRNAs as biomarkers of OSA in children, and also as biomarkers of cognitive deficits may further advance the field of biomarkers in sleep medicine [46], while enabling initial steps for a convenient diagnostic tool in children with suspected OSA that also carries enabling elements of precision medicine [74,75,76].

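### The 6-month AHI used as the effect in the non-inferiority test and the ICER does not penalise unnecessary treatment, and it dilutes missed OSA if all children are averaged

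*Protocol article*

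**What the plan says.** All quotations are from the protocol article.

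- **The test.** Section 3: "Cost effectiveness analysis is proposed as a non-inferiority study, comparing baseline PSG and 6-month follow-up PSG derived AHI (alpha 0.05; 80% power". The limit follows: "It is assumed that the non-inferiority limit is 0.45 units of AHI, i.e., the PSG AHI at 6 months follow-up for therapeutic decisions made" with PSG or HRP findings, "with a cut-off AHI set at 3.6 ± 2.0 events/h". The size is then given: "Considering attrition, 155 subjects will be required to complete the study in each arm (PSG and HPR".
- **The economic effect measure.** Section 3 states that costs "will be assessed against the effectiveness of the primary variable (AHI) using Bayesian cost-effectiveness analysis techniques". No other effect is named for the ICER.
- **Prevalence.** Section 3 assumes that 60% of the symptomatic children have an AHI above 3 events/h. It plans 320 children.
- **Who has the 6-month PSG.** Section 2.2.2 names randomized OSA children but also covers children who received no treatment. Section 2.7 says that children without OSA at the first study have an additional PSG.
- **Other analyses of errors.** Section 3 also plans diagnostic accuracy at the AHI cut-off of 3, ROC curves at several cut-offs, and Cohen's kappa between PSG-based and HRP-based therapeutic decisions. Treatment costs, including adenotonsillar surgery, are counted.
- **The stated purpose.** Section 4 says that the study assesses "when to provide clinical treatment and when to abstain from a therapeutic intervention".

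**The concern.** A diagnostic strategy can fail in two ways: it can lead to treatment of a child who does not have the disease, or leave a child who has it untreated. Follow-up AHI sees these very differently. A child without OSA who is treated needlessly still has a low AHI at 6 months, so that error counts as no loss or even a small gain. A missed case does raise the mean, but if everyone is averaged the rise is spread over the roughly 40% of children who have no OSA.

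At stake is the interpretation of the non-inferiority claim. The article promises to judge decisions to abstain as well as decisions to treat. The test that carries the claim about outcome after HRP-guided decisions cannot detect a failure to abstain. A larger sample or a different way of forming the arms would not change that.

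**Working it through.** **Inputs from Section 3.** Limit 0.45; SD 2.0 (reading 3.6 ± 2.0 as mean ± SD, although it is labelled a cut-off); alpha 0.05, sidedness not stated; power 80%; 155 per arm; prevalence 0.60; 320 children, hence 0.6 × 320 = 192 with OSA and 128 without.

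**Assumed, not in the document.** d = excess 6-month AHI of a missed child over the same child treated; g = reduction in AHI (0 or more) when a child without OSA is treated; SD constant at 2.0.

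**1. The plan's own figure.** In paired or one-sample form, n = (SD × (z_alpha + z_power) / limit)².

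- One-sided 0.025: (2.0 × (1.960 + 0.842) / 0.45)² = 155.04. This matches 155, with nothing added for attrition.
- One-sided 0.05: 122.1, so 123.
- Two independent arms need twice as many in each arm: 245 (0.05) or 311 (0.025). 155 per arm does not reproduce in that form.

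The document does not settle which form applies, so both are carried below. Standard errors at 155: two-arm 2.0 × √(2/155) = 0.227; paired 2.0/√155 = 0.161. The probability of passing at a true difference δ is Φ((0.45 − δ)/SE − z_alpha).

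**2. Unnecessary treatment.** If HRP leads to treatment of every child, the OSA children are managed as under PSG and the 40% without OSA are treated as well. Then δ = −0.4 × g, which is never above 0.

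| g | δ | two-arm, 0.05 / 0.025 | paired, 0.05 / 0.025 |
|---|---|---|---|
| 0 | 0 | 63% / 51% | 88% / 80% |
| 0.5 | −0.20 | 89% / 82% | 99% / 98% |
| 1 | −0.40 | 98% / 96% | about 100% / about 100% |

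The first row is also the pass rate of a strategy truly equal to PSG. Treating everyone therefore never passes less often than equivalence does.

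**3. Missed OSA, all children averaged.** δ = 0.6 × s × d. Setting this to 0.45 gives s = 0.75/d: 37.5% (72 of 192) at d = 2, 25% (48) at d = 3, 15% (29) at d = 5. These are the points where the true shift equals the limit, so the trial passes there only with probability alpha.

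For s = 25%, δ = 0.15 × d:

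| d | δ | two-arm, 0.05 / 0.025 | paired, 0.05 / 0.025 |
|---|---|---|---|
| 1 | 0.15 | 37% / 26% | 59% / 46% |
| 2 | 0.30 | 16% / 10% | 24% / 15% |
| 3 | 0.45 | 5% / 2.5% | 5% / 2.5% |
| 4 | 0.60 | 1% / 0.4% | 0.5% / 0.2% |

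For an even chance of passing at one-sided 0.05, δ must equal 0.45 − 1.645 × 0.227 = 0.08 (two-arm) or 0.45 − 1.645 × 0.161 = 0.19 (paired). At d = 3 that is s = 0.08/1.8, about 4%, or 0.19/1.8, about 10%.

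**4. Whether all children are averaged.** Section 2.7 gives children without OSA a 6-month PSG. If the arms are different children, 2 × 155 = 310 exceeds the 192 expected with OSA. If the comparison is paired within children, 155 would fit inside 192, so the head count alone does not settle it. In an analysis of OSA children only, δ = s × d and the limit is reached at s = 0.45/3 = 15% for d = 3. The dilution then disappears, but the children treated unnecessarily drop out of the test altogether.

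**The case against.** **The trial as a whole is not blind to these errors.** A reader might infer that it is, and the document does not support that. Diagnostic validity is the main objective. Accuracy and ROC analyses separate false positives from false negatives, HRP-based and PSG-based decisions are compared directly, and surgery and other treatments are costed, so treating everyone would worsen the ICER through its cost side. This stands. What remains is that kappa is one undirected number, ROC describes the test result rather than the decision taken, and neither is stated to inform the non-inferiority conclusion. In the costs, visits related to adenotonsillar surgery are excluded from later health care.

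**Missing a quarter of cases would not generally be accepted.** It is tempting to read 25% as what the limit tolerates. It is the point of failure at d = 3, and the strategy fails more surely at larger d. Only small d, as with mild cases near the cut-off, gives a material pass rate.

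**Affected children need not stay untreated in this trial.** Section 2.2.2 has a safety board that reviews both tests and corrects inappropriate decisions. This bears on harm to participants. It does not help the endpoint: correction would shrink the AHI difference further.

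**A 6-month patient outcome is a legitimate endpoint for a test-and-treat strategy.** That is so. Scoring decisions only against PSG would make PSG right by construction, and a new main endpoint would need a new limit and sample size. This argues against replacing the AHI test, not against adding to it.

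**Conclusion.** The point holds in limited form. In the 0.45 non-inferiority test and the ICER effect term, unnecessary treatment costs nothing and may earn credit. This needs only the assumption that treatment does not raise AHI, and no value of d. The dilution of missed OSA by the factor 0.6 holds if all children are averaged, which Section 2.7 supports but Section 3 does not state; that the quantity is a mean is likewise inferred from the ± notation. Missing a quarter of OSA cases passes in about 10–37% (two-arm) or 15–59% (paired) of trials at d of 1 to 2, and only at the alpha level at d = 3.

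The document does not support the stronger conclusions that the trial cannot see wrong decisions at all, or that it would be expected to declare a strategy missing a quarter of cases non-inferior.

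A separate matter must be reconciled between Sections 2.2.2 and 3: all treatment follows HRP with board correction, yet the test refers to 6-month AHI after decisions made on PSG.

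**What to change.** Keep the 6-month AHI test and its limit, state the population in which it is analysed, and add three things:

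1. **Two decision-error rates beside kappa, with confidence intervals.** Against the decision from baseline PSG, report the share treated on HRP but not on PSG, and the share not treated on HRP but treated on PSG. Use the HRP decision as recorded before any board correction. State that the non-inferiority conclusion will be interpreted together with these rates.
2. **An analysis in children with OSA on baseline PSG.** Report their 6-month AHI and the proportion with residual OSA at the plan's own cut-off, so that missed cases are not diluted.
3. **Cost per correctly managed child as a sensitivity analysis.** It should not replace the main ICER, because PSG is correct by construction on that scale.

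The HRP-based and PSG-based decisions and both PSGs are already planned, so no new measurement is needed. The pre-correction HRP decision has to be kept in the data. The cost is a little more analysis and the possibility that a non-inferiority claim must be qualified.

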## Abstract

Obstructive sleep apnea (OSA) in children is a prevalent, albeit largely undiagnosed disease associated with a large spectrum of morbidities. Overnight in-lab polysomnography remains the gold standard diagnostic approach, but is time-consuming, inconvenient, and expensive, and not readily available in many places. Simplified Home Respiratory Polygraphy (HRP) approaches have been proposed to reduce costs and facilitate the diagnostic process. However, evidence supporting the validity of HRP is still scarce, hampering its implementation in routine clinical use. The objectives were: Primary; to establish the diagnostic and therapeutic decision validity of a simplified HRP approach compared to PSG among children at risk of OSA. Secondary: (a) Analyze the cost-effectiveness of the HRP versus in-lab PSG in evaluation and treatment of pediatric OSA; (b) Evaluate the impact of therapeutic interventions based on HRP versus PSG findings six months after treatment using sleep and health parameters and quality of life instruments; (c) Discovery and validity of the urine biomarkers to establish the diagnosis of OSA and changes after treatment.

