## 1. Introduction

Obstructive sleep apnea (OSA) is a common disorder of children characterized by habitual snoring, prolonged episodes of increased upper airway resistance, and respiratory effort with partial or complete upper airway obstruction during sleep. OSA is accompanied by different degrees of intermittent hypoxemia and hypercapnia and can lead to sleep fragmentation [1,2,3,4]. OSA affects 1–4% of children with a peak incidence around 2–8 years [1,2,4] and most of children with OSA are under-recognized [5]. The severity of OSA is measured by the apnea-hypopnea index (AHI), whereby most centers consider a AHI ≥ 3 events/h as clinically significant, and will routinely initiate treatment [1,2]. In the last several decades since its initial description, OSA has been associated with a large spectrum of neurocognitive, behavioral, cardiovascular, and metabolic adverse consequences, and it has been assumed that timely recognition of OSA and its resolution through adequate treatment would eventually reverse or prevent these consequences [5,6,7]. The most effective treatment of OSA in children consists in surgical adenotonsillectomy (T&A), although several alternative treatments have been developed in recent years [6,7].

The recommended diagnostic approach of OSA in children consists in conventional overnight polysomnography (PSG) in the sleep laboratory [8]. However, PSG is expensive, time-consuming, and inconvenient for patients and parents. In addition, children and caretakers are required to spend the night in the laboratory, an unfamiliar environment that can generate anxiety and alter sleep architecture. On the other hand, PSG is not readily available in many places around the world, and the overall number of professionals with expertise in sleep medicine further restricts the accessibility, leading to substantial delays and waiting times [9]. 

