Apnea-Link Air (Resmed^®^Spain) is a simplified polygraphic recording device designed for domiciliary use. It consists of a nasal canula with a pressure transducer, with thoracic and abdominal effort being measured by plethysmography, and oxyhemoglobin saturation by continuous pulse oximetry. The proprietary software of the device allows for both automatic and manual analysis of the physiologic signals. Its use has been validated in adults [39,40,41], but its utility in children has yet to be explored.

In the quest to develop simplified approaches to the diagnosis of OSA in children and potentially identify OSA-associated morbidities, exploration of biomarkers was pioneered about a decade ago, with overall encouraging findings [42,43,44,45,46,47,48,49,50,51,52]. Indeed, a large number of candidate biomarkers consisting of proteins and microRNAs have emerged, and have provided important insights into potential mechanisms underlying OSA-associated morbidities while also displaying favorable diagnostic profiles. 

Based on aforementioned considerations, the present study protocol was designed to address several critically important issues aimed at facilitating access to symptomatic children at risk for OSA, enabling their diagnosis at home, identifying associations with pragmatically applicable cognitive testing, identify exosomal miRNA markers in their urine, and ultimately allow for evaluation of their treatment outcomes. 

The main objective of the study was to assess the diagnostic validity of a HRP, specifically the Apnea-Link Air system, in children with clinically suspected OSA, and compare the findings with concurrent PSG results. 

The secondary outcomes of the proposed study were to:Analyze the cost-effectiveness of HRP compared with PSG.To determine the validity of diagnostic and therapeutic decisions using the results of HRP findings based on either manual scoring or automatic analysis, compared to decisions using PSG results.To identify and analyze the validity urine biomarkers in the diagnosis and in identification of cognitive morbidity among children with OSA children and their changes after OSA treatment.

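### Cohen's kappa is the only statistic named for therapeutic decisions, and it cannot show whether HRP misses needed treatment or prompts unneeded treatment

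*Protocol article*

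**What the plan says.** The Statistical Analysis section of the protocol article states: "Therapeutic decisions made with PSG will be compared with decisions made with HPR, with data being interpreted independently by all participating centers". The sentence ends by saying that they are "compared with each other using Cohen’s Kappa". It gives no weighting, no acceptance threshold and no separate rate for either kind of disagreement.

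The standing of this objective differs within the article. The Abstract makes it part of the primary objective: "to establish the diagnostic and therapeutic decision validity of a simplified HRP approach compared to PSG among children at risk of OSA". The Introduction lists it among the secondary outcomes: "To determine the validity of diagnostic and therapeutic decisions using the results of HRP findings based on either manual scoring or automatic analysis". The Study Significance section describes the aim as the robustness of HRP in "clinical decision making of when to provide clinical treatment and when to abstain from a therapeutic intervention".

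For diagnosis, as distinct from the treatment decision, the same Statistical Analysis section plans diagnostic accuracy at the AHI cut-off, for automatic and manual scoring, and ROC curves at several severity cut-offs. The section on randomization and follow-up names four kinds of treatment (adenotonsillectomy, CPAP, orthodontics, medical), so the decision is not purely binary.

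**The concern.** Kappa measures agreement between two raters of equal standing. Here the PSG decision is the reference, and the two ways of disagreeing with it have different consequences: a child whose PSG decision is to treat goes untreated, or a child whose PSG decision is not to treat is treated, possibly by surgery. Kappa pools the two. It also depends on how many children are treated, so the same HRP error rates give different values in different case mixes.

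The aim has two halves, treating and abstaining, and a single symmetric index answers neither. A reader given only kappa could not tell which way HRP errs. Direction matters here because HRP divides events by total recording time and PSG by total sleep time, and because arousals are identified only on PSG. Both features would tend to lower the HRP index, so one-sided error is plausible, though the article gives no figure for its size.

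**Working it through.** The article states no kappa value, target or sample size for kappa, so there is no planned figure to reproduce.

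**Inputs**
- Completers: 320 less 10% attrition = 288 (Statistical Analysis).
- Share treated on PSG: 60%. This is an assumption. It takes the stated prevalence ("We estimated a prevalence of 60% of symptomatic children with an AHI > 3 events/h") as the treated share, supported by the Introduction's remark that "most centers consider a AHI ≥ 3 events/h as clinically significant, and will routinely initiate treatment". It gives 0.60 × 288 ≈ 173 treat and 115 not treat.
- The decision is collapsed to treat or not treat.

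**Formula.** Let p be the PSG treat share, m the proportion of PSG-treat children missed by HRP, and u the proportion of PSG-no-treat children treated on HRP.
- Observed agreement: po = 1 − p·m − (1 − p)·u
- HRP treat share: q = p(1 − m) + (1 − p)u
- Chance agreement: pe = p·q + (1 − p)(1 − q)
- kappa = (po − pe)/(1 − pe)

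**Three tables with the same 29 disagreements** (po = 259/288 = 0.899 in each)

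| Missed | Unnecessary | HRP treats | pe | kappa | Missed, of 173 | Unnecessary, of 115 |
|---|---|---|---|---|---|---|
| 29 | 0 | 144 | 0.500 | 0.80 | 16.8% | 0% |
| 0 | 29 | 202 | 0.541 | 0.78 | 0% | 25.2% |
| 15 | 14 | 172 | 0.520 | 0.79 | 8.7% | 12.2% |

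First row: (0.899 − 0.500)/(1 − 0.500) = 0.80. Second row: (0.899 − 0.541)/(1 − 0.541) = 0.78.

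Simulated 95% ranges for kappa at n = 288, with exactly 10% of all children misclassified in one direction, overlap almost fully: 0.73 to 0.87 for missed treatment only, 0.71 to 0.85 for unnecessary treatment only.

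Exchanging the two disagreement cells of a 2×2 table leaves kappa exactly unchanged. The small differences above arise only because the PSG totals are held at 173 and 115. Weighting would not help: with two categories, weighted and unweighted kappa coincide.

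**Range over the assumed treat share**

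| PSG treat share | Misses 1 in 6 of PSG-treat | Treats 1 in 4 of PSG-no-treat |
|---|---|---|
| 40% | 0.86 | 0.71 |
| 50% | 0.83 | 0.75 |
| 60% | 0.80 | 0.78 |
| 70% | 0.75 | 0.81 |
| 80% | 0.67 | 0.83 |

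Each column holds the error rates fixed. The change down a column is case mix alone.

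**What direction-specific measures show.** Wilson 95% intervals: 29/173 = 16.8% (11.9% to 23.0%); 29/115 = 25.2% (18.2% to 33.9%). McNemar's statistic, (missed − unnecessary)²/(missed + unnecessary), is 29²/29 = 29 for either one-sided table and 1²/29 = 0.03 for the 15/14 split. The proportions and the test separate three situations that kappa places between 0.78 and 0.80.

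**The case against.** The best case for the plan has five parts.

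- **Directional analyses are already planned.** Decisions rest on the HRP index. If treatment followed AHI > 3 exactly, sensitivity and specificity at that cut-off would be the complements of the two proportions proposed here. This stands in part: a reader might infer that the plan is blind to direction altogether, and it is not. But those analyses are defined on the index and the diagnosis. They equal the decision error rates only if the decision is nothing more than crossing the cut-off.
- **No threshold is set.** A reader might infer that a kappa near 0.8 would be taken as proof of validity. The article says no such thing; 0.8 is only this illustration's value.
- **The near-equality is local.** A reader might infer that the two error patterns always look alike on kappa. The range table shows that, at these error rates, they do so only near a 60% treat share. The denominators matter too: the figures refer to one in six of PSG-treat children and one in four of PSG-no-treat children, each about 10% of the whole sample. Taken over all children, the same fractions would give kappas of 0.68 and 0.42.
- **Kappa has legitimate uses here.** The sentence can also be read as covering agreement between centres, and there are several treatment types. Kappa suits both, which is a reason to keep it.
- **Other safeguards and an unseen SAP.** A Safety Monitoring Board reviews both tests and corrects inappropriate decisions, and six-month AHI is compared. Neither is stated to report the two error rates, and correction by the Board can keep a wrong HRP decision from showing in later outcomes. An SAP could well display the cross-table, but the article does name a statistic, and the one it names does not fit the question.

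**Conclusion.** The point holds as a cheap improvement to the choice of measure; it does not show a wrong result or a contradiction in the analysis. The only statistic named for the treatment decision cannot separate missed from unnecessary treatment and shifts with the share treated. Its size, assuming 288 completers, a 60% PSG treat share and a binary decision, is that 29 one-sided errors give kappa 0.80 or 0.78 depending on direction. The symmetry of kappa does not rest on those assumptions; the closeness of the two values does. The weight of the point depends on whether decision validity is primary, as in the Abstract, or secondary, as in the Introduction. The documents do not support the stronger inference that HRP will in fact under-treat: the direction is plausible from how the two indices are derived, but its extent is not given.

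**What to change.** For the treat/no-treat decision, with the PSG decision as reference, name two lead measures:

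1. the missed-treatment proportion among children whose PSG decision is to treat;
2. the unnecessary-treatment proportion among children whose PSG decision is not to treat.

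Give each a 95% CI, add McNemar's test for direction, and report everything separately for manual and automatic HRP. McNemar's test compares the two error counts, so it supplements the proportions and does not replace them.

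Keep kappa, with the full cross-table of treatment types, as a secondary descriptive measure of agreement on type of treatment and between centres. The binary measures do not capture disagreement about which treatment is chosen.

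Cost: a change of wording only, using data already planned. The downside is two figures in place of one, each estimated on part of the sample and so less precise (for example 29/173, 95% CI 11.9% to 23.0%).
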